## Abstract

People who use illicit drugs (PWUDs) have been identified as a key at-risk group for tuberculosis (TB). Examination of illicit drug use networks has potential to assess the risk of TB exposure and disease progression. Research also is needed to assess mechanisms for accelerated TB transmission in this population. This study aims to 1) assess the rate of TB exposure, risk of disease progression, and disease burden among PWUD; 2) estimate the proportion of active TB cases resulting from recent transmission within this network; and 3) evaluate whether PWUD with TB disease have physiologic characteristics associated with more efficient TB transmission. Our cross-sectional, observational study aims to assess TB transmission through illicit drug use networks, focusing on methamphetamine and Mandrax (methaqualone) use, in a high TB burden setting and identify mechanisms underlying accelerated transmission. We will recruit and enroll 750 PWUD (living with and without HIV) through respondent driven sampling in Worcester, South Africa. Drug use will be measured through self-report and biological measures, with sputum specimens collected to identify TB disease by Xpert Ultra (Cepheid) and mycobacterial culture. We will co-enroll those with microbiologic evidence of TB disease in Aim 2 for molecular and social network study. Whole genome sequencing of *Mycobacteria tuberculosis* (*Mtb*) specimens and social contact surveys will be done for those diagnosed with TB. For Aim 3, aerosolized *Mtb* will be compared in individuals with newly diagnosed TB who do and do not smoke illicit drug. Knowledge from this study will provide the basis for a strategy to interrupt TB transmission in PWUD and provide insight into how this fuels overall community transmission. Results have potential for informing interventions to reduce TB spread applicable to high TB and HIV burden settings.

**Trial registration:** Clinicaltrials.gov Registration Number: NCT041515602. Date of Registration: 5 November 2019.

## Introduction

Tuberculosis (TB) is one of the leading infectious diseases globally that cause death, including among people living with HIV (PLHIV) [1]. An effective method to reduce TB incidence and mortality is to interrupt transmission, which requires finding and treating individuals with subclinical and clinical TB disease early. Molecular epidemiologic studies and mathematical models have shown that household contact tracing, our primary approach to case finding, identifies less than 19% of transmissions in high TB and TB/HIV burden settings [2]. There is a clear need to identify additional risk groups and settings where TB transmission occurs. New approaches have focused on congregate settings, such as prisons and healthcare facilities, to identify additional TB transmission [3]. A major source of transmission also may exist in venues where individuals smoke illicit drugs, making these social networks potential amplifiers for the broader population epidemic and a group to target for transmission interventions.

Globally, people who use drugs (PWUD) have higher TB infection prevalence and disease incidence compared to people who do not use drugs, likely reflecting a combination of within-group transmission and clustered vulnerability [4]. In the US, nearly one third of persons ≥ 15 years old with TB disease reported problem alcohol or drug use [5], and the majority of US-based outbreaks between 2002 and 2015 were among PWUD. TB outbreaks among PWUD have also been reported in other countries [6–11]. In the past 20 years, TB incidence has decreased in most high-income countries with TB disease burden concentrated in at-risk subpopulations, including PWUD [12]. Similar higher rates of TB disease among PWUD may occur in high TB burden settings as well, reflecting increased transmission within these groups, but the phenomenon may be harder to isolate given the general high population burden.

South Africa is an ideal context to study the relationship between drug use and TB due to its concurrent high TB/HIV burden and high drug use prevalence [13, 14]. Nationally, an estimated 13.3% of the adult population meet criteria for a lifetime substance use disorder (SUD), with rates as high as 20.6% for the Western Cape Province [14]. Community-based data related to illicit drug use in South Africa are limited but suggest a growing problem. A 2012 population-based study of adults found the past 3-month prevalence was 4.0% for cannabis, 0.4% for sedatives, and 0.3% for amphetamines [13]. A 2017 national study estimated the prevalence of any drug use in the last 3 months increased to 8.6% of adults, largely driven by cannabis use followed by Mandrax (methaqualone) and stimulants such as methamphetamine [15]. Polysubstance use is common [16, 17], and likely to be under-reported due to the illicit nature of substance use and concerns about stigma. In the Western Cape, methamphetamine (referred to as tik), which is generally smoked, has been a popular self-reported drug of choice among patients entering SUD treatment for a number of years.

PWUD, particularly those who smoke drugs, may be especially efficient TB transmitters, due to the sharing of pipes and other drug equipment, and time spent in close, poorly ventilated settings [6]. Physiological effects of smoked drugs induce repeated coughing and lung trauma, which likely facilitates TB spread [18, 19]. Illicit drug use also frequently co-occurs with other TB disease risk factors, including tobacco and alcohol use, HIV, and environmental risk factors such as homelessness, malnutrition, and incarceration history [6, 20–23]. Symptoms of regular drug use, including chronic cough, weight loss, and sweats, also often overlap with TB symptoms, leading to delayed evaluation [24, 25]. In addition, PWUD often wait longer to present for treatment due to perceived stigma or fear of withdrawal, especially if hospitalized [26]. Routine TB investigations and contact tracing may miss links between PWUD due to underreporting of relationships which involve drug use or sales [27]. Hereafter, PWUD refers to those who smoke illicit drugs (rather than inject or ingest).

Respondent Driven Sampling (RDS), developed to understand and address infectious disease epidemics in hard-to-reach or hidden populations [28, 29], may be effective for recruiting PWUD into community-based TB studies and provide opportunities to understand social dynamics of TB transmission. RDS uses coupons with unique numbers to track recruitment, incentives for survey participation and for recruiting others into study activities and is initiated by purposively selecting initial members of the target population, known as *seeds*. A variant of chain referral sampling, RDS has the advantage of using statistical estimation methods to limit biases from peer-driven recruitment [29]. While RDS has successfully reached and recruited PWUD [30, 31] to understand drug use, involvement in illegal activities, and HIV risk behaviours in Cape Town’s peri-urban communities, it has not been widely utilised in rural settings or for TB transmission studies. In preparation for RDS, formative work was conducted with eight focus groups with participants from the study’s target population, namely, individuals who self-reported current methamphetamine and/or Mandrax use, to obtain recommendations for recruitment, confirm whether RDS would be a feasible strategy and identify potential seeds.

### Primary objectives

The Transmission Of Tuberculosis Among illicit drug use Linkages (TOTAL) study has three aims. The first is to assess the TB exposure, risk of disease progression, and disease burden among PWUD, including people living with and without HIV. We hypothesize that TB prevalence in PWUD will be significantly higher compared to results from a community-wide survey [32] and that the prevalence of incipient TB (host RNA signature presence) will be significantly higher among PWUD compared to the general community. We also hypothesize that PWUD living with HIV will have higher rates of incipient, subclinical, and clinical TB disease compared to those PWUD who are HIV negative.

Second, we aim to estimate the proportion of active TB cases that are the result of transmission within the social network of PWUD. We hypothesize that there will be a high proportion of linked isolates from Aim 1, reflecting predominance of recent transmission within this cohort. We also expect that persons with TB/HIV co-infection will more often appear as contacts with fewer links compared to persons with TB disease alone, reflecting their increased susceptibility to TB and their decreased ability to transmit TB.

Third, we aim to evaluate whether PWUD with TB disease have physiologic characteristics associated with more efficient TB transmission compared to people with TB disease who do not use drugs. Among individuals with TB, we hypothesize that PWUD will produce larger amounts of aerosolized *Mtb* than people who do not use drugs, after adjusting for bacterial burden (tested by mycobacterial culture time to positivity and GeneXpert Ultra). We will include people with and without HIV in each arm to assess any modifying effects of HIV, and record other smoked substances (tobacco, cannabis) and alcohol use to assess their impact as well.

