### Participant eligibility criteria

Study participants will be recruited by referral chains of PWUD that start with seeds who will be ≥15 years old, reside locally, are willing and able to provide written informed consent and participate in study activities. Inclusion criteria by study arm in shown in Fig 2. For Aim 1, additional inclusion criteria will include self-reported methamphetamine or Mandrax use in the past month and a positive urine drug screen for either of these drugs at enrollment, and a coupon indicating their recruitment into the study by another participant (with the exception of seeds). For Aims 2 and 3, individuals will have microbiologic evidence of active TB disease Xpert Ultra (Cepheid, CA) or *Mtb* culture]. For Aim 3, participants will be excluded if they are pregnant, have taken >5 days of TB medication, or for the control group in Aim 3 Arm 2, if they self-report any past month drug use or have positive urine drug test results. Exclusion criteria for all study aims will include current alcohol or drug intoxication and inability to provide informed consent.

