### Recruitment and assessment of primary objectives

For Aim 1, we will invite eligible participants to enroll as initial study participants (seeds).

Individuals will provide written informed consent (and parental consent will be obtained for individuals <18 years) before being screened for Aim 1 eligibility. Enrollment will include the collection of biometric fingerprints. Seeds will then complete interviewer-administered biobehavioural questionnaires and provide blood for COVID-19 serology, rapid HIV testing, and host RNA sequencing, and induced sputa for Xpert Ultra and mycobacterial culture respectively. Those with a new HIV diagnosis will be referred to a clinic so that they can access HIV care services. For the latter, sputum will be liquefied and decontaminated (N-Acetyl-L-Cysteine) and neutralized in PBS. The bacilli will be collected by centrifugation, with positive MGIT cultures assessed for acid fast bacilli and Capilia TB Testing to confirm the *Mtb* presence.

Each seed will then be given two coupons to recruit two people with whom they currently use methamphetamine and/or Mandrax. The initial recruits who are successfully enrolled into the study will be given two recruitment coupons to disperse in the same manner. This will continue until we reach 750 participants. Additional seeds will be included as needed until we reach the target sample size (n = 750).

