### RNA sequencing

RNA will be extracted from PAXgene tubes collected during Aim 2 or Aim 3 Arm 2 study procedures, and complimentary or cDNA prepared using an automated mRNA extraction, which would be done with a Hamilton EasyBlood Star at Stellenbosch University and cDNA synthesis procedure together with the PAXgene Blood RNA Kit (Qiagen, Germany). We will use the Fluidigm microfluidic qRT-PCR platform to evaluate the expression of genes selected from different published TB transcriptomic biosignatures, using TaqMan primer-probes. Assays will be run on either the 96.96 or 192.24 Gene Expression chips (Fluidigm) on a Biomark HD multiplex microfluidic qRT-PCR instrument. Analysis of gene expression data, including PCR controls and assessment of internal quality control samples to monitor performance of assays across individual Gene Expression chips, and computation of signature scores will be done with pre-prepared R scripts [39–41]. We will look for prevalence of the 16-gene host RNA signature previously studied by other research institutes in Worcester [32, 42], as well as other available signatures shown to be associated with higher risk of disease progression.

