### Data analysis

#### Sample size assumptions

For Aim 1, our estimated sample size of 750 individuals using RDS was calculated based on feasibility. Previous work suggests PWUD compared to non-users have a 2–6 fold increase in TB prevalence, translating into potentially detecting 30–90 TB cases from Aim 1 [12]. TB prevalence among the general population is estimated to range between 1–4% [32]. We assumed prevalence of drug use at 2.6% in the general population [54] and an estimated design effect (DE) of 4 allowing us to detect a three-fold increase in prevalence to 7.2% for PWUD with 80% power; if DE = 2 we can detect a two-fold increase to 5.7%. We therefore concluded that this sample size was appropriate under a variety of reasonable assumptions. Our sample size continues to provide 80% power if prevalence increases to 3%. The incipient disease signature prevalence in the community has been estimated at 13%, meaning that we have 80% power to detect a 1.4 (DE = 2) or 1.5 (DE = 4) fold increase in incipient disease among PWUD.

For Aim 2, other studies have consistently estimated that individuals who are in close contact with one another are linked by WGS in more than 70% of the sample [55]. If this is the case among PWUD, then for a sample size of 50 individuals, our precision will be 24.6% meaning our 95% confidence interval (CI) will range from 56.2% to 80.9%.

Patterson et al. found that 43% of individuals who had tested positive for drug-sensitive pulmonary TB by with Xpert Ultra had positive cough aerosols and those with non-zero colony forming units (CFU) measuring bacterial load had a median of 2.5 CFU [38]. Assuming that this is similar in controls, this would mean that by enrolling of 50 PWUD and 50 controls for Aim 3, we have 80% power to detect a 70% positive CFU probability in PWUD. Among those positive, we have 80% power to detect a 2.5-fold increase in the median CFU value with Mann-Whitney test and assuming CFU values are exponentially distributed. Similarly, assuming exhalation pattern frequency of 23.9 in controls, we have 80% power to detect a 2-fold increase in median exhalation frequency between PWUD and controls to enable us to demonstrate good power for the hypothesized drug use effect.

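### Incipient TB is defined by host RNA signature alone, so participants with confirmed TB can be counted as incipient, inflating the PWUD–community contrast

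*Protocol article*

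**What the plan says.** All references are to the protocol article.

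- **Primary objectives** states two Aim 1 hypotheses against the community. One concerns TB disease: "We hypothesize that TB prevalence in PWUD will be significantly higher compared to results from a community-wide survey". The other concerns the signature: "the prevalence of incipient TB (host RNA signature presence) will be significantly higher among PWUD compared to the general community". A third hypothesis is internal to the sample: "PWUD living with HIV will have higher rates of incipient, subclinical, and clinical TB disease" than HIV-negative PWUD.
- **Sample size assumptions** carries the same equation of signature with incipient disease: "The incipient disease signature prevalence in the community has been estimated at 13"%, with 80% power claimed for a 1.4-fold (DE = 2) or 1.5-fold (DE = 4) increase. For active TB it takes a 2–6 fold excess from previous work, "translating into potentially detecting 30–90 TB cases from Aim 1".
- **Participant eligibility criteria** does not list active TB as a reason for exclusion from Aim 1: "Exclusion criteria for all study aims will include current alcohol or drug intoxication and inability to provide informed consent".
- **Recruitment and assessment of primary objectives** has participants "provide blood for COVID-19 serology, rapid HIV testing, and host RNA sequencing, and induced sputa for Xpert Ultra and mycobacterial culture respectively". Table 1 lists both the RNA blood and the sputum under Aim 1.
- **RNA sequencing** describes a different source of samples: "RNA will be extracted from PAXgene tubes collected during Aim 2 or Aim 3 Arm 2 study procedures".
- **Substance use and biobehavioural measures** separates clinical from subclinical TB by symptom screen. No section separates incipient TB from either.

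**The concern.** Naming three states implies that each person belongs to one of them. The only working definition given for incipient TB is that the signature is present, and a person with a positive culture can also have the signature. Followed as written, that person counts once as a TB case and again as an incipient case.

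The double counting is not neutral between the groups. The plan expects active TB to be commoner in PWUD than in the community. If the signature is commoner in active TB than in TB-free people, signature prevalence in PWUD rises for that reason alone. A significant result could then be read as greater risk of progression, which is a named part of Aim 1, when some or all of it repeats the TB prevalence finding. The HIV contrast on incipient TB has the same defect in kind, because more active TB is also expected in PWUD with HIV.

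**Working it through.** **1. The plan's own figure.** Inputs: n = 750, reference p0 = 0.13, 80% power, DE 2 or 4. Alpha and sidedness are not stated; I assume 0.05 two-sided. The test is one-sample against a fixed 13%, using the null variance:

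fold = 1 + (1.960 + 0.842) × √(p0(1 − p0)/n_eff) / p0

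- DE 2: n_eff = 375, fold = 1.37.
- DE 4: n_eff = 187.5, fold = 1.53.

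These match the stated 1.4 and 1.5 at one decimal.

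**2. Contribution of active TB alone.** Let c be community TB prevalence, p TB prevalence in PWUD, s signature positivity in active TB, and u signature positivity in TB-free people. Set u equal in both populations, so that there is no true excess of incipient TB.

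u = (0.13 − c·s)/(1 − c); PWUD signature prevalence q = p·s + (1 − p)·u; apparent fold = q/0.13

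Inputs:

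- p = 5.7% and 7.2%: the plan's powered alternatives.
- p = 10%: 75/750, the upper Aim 2 projection in Methods.
- p = 12%: 90/750, the top of the range in Sample size assumptions.
- c = 2.6%: **an assumption**. The article gives 1–4% for community TB, and attaches the figure 2.6% to drug use.
- s = 50–90%: **an assumption**. The documents give no value.

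With c = 0.026, u is 0.1201, 0.1148 and 0.1094 for s = 0.5, 0.7 and 0.9. Worked case, p = 0.12 and s = 0.7: q = 0.084 + 0.88 × 0.1148 = 0.185, fold = 1.42.

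| TB in PWUD | s = 50% | s = 70% | s = 90% |
|---|---|---|---|
| 5.7% | 1.09 | 1.14 | 1.19 |
| 7.2% | 1.13 | 1.21 | 1.28 |
| 10% | 1.22 | 1.33 | 1.45 |
| 12% | 1.27 | 1.42 | 1.57 |

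Sensitivity at 12% TB with s = 70–90%: c = 2% gives 1.45–1.60 and c = 4% gives 1.37–1.49. If s is only 13%, there is no distortion. If the 13% reference already refers to TB-free people (u = 0.13), the ranges for s = 50–90% become 1.20–1.43 at 7.2% and 1.34–1.71 at 12%.

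**3. False-positive rate.** This is the probability of a significant upward result at two-sided 5% when there is no excess of incipient TB. The 13% is treated as an all-comers figure, c = 2.6% and s = 50–90%:

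Φ[(q − 0.13 − 1.96·√(0.13 × 0.87/n_eff)) / √(q(1 − q)/n_eff)]

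| TB in PWUD | DE 2 | DE 4 |
|---|---|---|
| 7.2% | 18–55% | 12–33% |
| 12% | 54–97% | 32–81% |

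The nominal rate is 5% over both tails.

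**4. Power after restriction.** Removing 30–90 cases leaves 660–720 people. With the step 1 formula and p0 still 13%, the detectable fold is 1.38–1.40 (DE 2) or 1.54–1.56 (DE 4). If the TB-free reference is lower than 13%, it is somewhat larger. With p0 = 0.1148 and 696 people (7.2% TB removed), √(0.1148 × 0.8852/348) = 0.0171 gives 1 + 2.802 × 0.0171/0.1148 = 1.42 at DE 2; the same step with n_eff = 174 gives 1.59 at DE 4.

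**The case against.** The parenthesis in the hypothesis could be naming the biomarker rather than giving a full case definition, and the three-state list suggests that separation was intended. A full protocol or SAP may hold the assignment rule. This has some force, but the equation of signature with incipient disease is used again in the power statement, and nothing shown restricts it. The stated rule conflicts with the article's own three states, which is more than missing detail.

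The second objection is that the size rests on figures outside the documents. That stands. Signature positivity in active TB is not given; the article links the signatures to risk of progression and says nothing on how often they are positive in confirmed TB. Using 2.6% for community TB is also an assumption.

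Third, if the 13% is an all-comers figure, the comparison as planned is like for like as a comparison of signature prevalence, and restricting only PWUD would create a new mismatch. That also stands, and it limits the fix. It does not rescue the label: TB prevalence differs between the groups, so all-comers signature prevalence still mixes active with incipient disease.

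A reader might go further and infer that the whole detectable effect is likely to be an artefact. The documents do not support that. At the powered alternatives of 5.7% and 7.2% TB, the artefact is at most 1.19 and 1.28 fold with an all-comers reference, below 1.4. At 12% TB and 50% positivity it is 1.27. Nor can the size of the HIV distortion be inferred, since TB prevalence by HIV status among PWUD is not given.

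**Conclusion.** The point holds in this form: the stated definition of incipient TB admits participants with confirmed TB, contradicts the article's separation of states, and biases the PWUD–community contrast upward if the signature is commoner in active TB. Under the assumptions in the working and an all-comers 13%, the bias is moderate at 7.2% TB in PWUD. It reaches the detectable 1.4–1.5 fold only near the top of the plan's TB range and with positivity of roughly 70% or more. Elsewhere its effect is an inflated estimate and an inflated false-positive rate, not a guaranteed significant result. Whether the 13% includes active TB is unknown; if it does not, the distortion is larger. The TB prevalence analysis itself is unaffected.

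A linked contradiction also needs resolving. RNA sequencing takes its tubes from Aim 2 or Aim 3 Arm 2, both groups with microbiologic evidence of TB. Recruitment and assessment of primary objectives and Table 1 put the RNA blood in Aim 1, and Table 1 lists no blood under Aim 2. Read literally, the RNA section would leave no TB-negative participants in whom to measure incipient TB.

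**What to change.** 1. Define incipient TB as signature-positive and negative on enrolment Xpert Ultra and culture, with microbiologically negative participants as the denominator. Use this for the comparison of PWUD with and without HIV.
2. Use the same definition for the community contrast only if the community figure can be obtained on a TB-negative basis. If only an all-comers figure exists, compare all-comers with all-comers and call the result signature prevalence, not incipient TB.
3. State whether the 13% includes people with active TB, and restate the detectable fold on the matching basis.
4. Reconcile the RNA sequencing section with the Aim 1 procedures and Table 1 on whose RNA is analysed.

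If RNA blood is taken from all Aim 1 participants, as Table 1 indicates, no new data are needed from PWUD. The denominator loses about 30–90 people. By the same formula and with a 13% reference, the detectable fold moves from 1.37 to 1.38–1.40 (DE 2) and from 1.53 to 1.54–1.56 (DE 4). The observed fold increase would be expected to be smaller, because active cases no longer contribute to it.
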